## Abstract

**Abstract:**

**Introduction:**

Adolescents living with HIV (ALHIV) are an extremely vulnerable population, with the burden of mental health problems carefully documented together with the constraints for receiving timely and adequate management of the problems, especially in rural settings. Problem Management Plus (PM+) is a scalable psychological intervention for individuals impaired by distress in communities exposed to adversity. Initially developed for adult populations, few studies have assessed its potential to address adolescent distress. This study aims to co-adapt PM+ with an adherence component (PM+Adherence) for ALHIV and to evaluate its acceptability and feasibility in rural Kwa-Zulu Natal Province, South Africa.

**Methods and analysis:**

We will use a mixed-methods approach over three phases. The first phase will include a realist synthesis and collection of formative data from up to 60 ALHIV, caregivers and healthcare providers to inform the adaptation of WHO PM+, including the components of an adherence module. During the second phase, we will undertake the cultural adaptation of the PM+Adherence intervention. The third phase will involve a hybrid type 3 implementation strategy among ALHIV aged 16–19 years (n=50) to implement and evaluate the feasibility of the culturally co-adapted PM+Adherence. The feasibility indicators to be evaluated include reach, adoption, attrition, implementation and acceptability of the adapted intervention, which will be assessed qualitatively and quantitatively. In addition, we will assess preliminary effectiveness using an intention-to-treat approach on HIV-related indicators and mental health outcomes at baseline, end intervention, 2-month follow-up during the 6-month implementation.

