### Data collection and management

The data collection schedule is presented in table 1. In this phase, data collection will be conducted through repeated assessment interviews at baseline (month 0), the end of the intervention (month 4) and 2 months after the intervention ended (month 6).

The questionnaires will be self-administered and collected via a tablet computer using Research Electronic Data Capture (REDCap) tools. The forms will be checked for completeness by a research assistant soon after completion, and errors will be corrected. The REDCap database resides within a single MySQL database server within a secure server cluster at AHRI. Interviews will be audio recorded and transferred into a password-protected computer for transcription.

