#### Quantitative data

Secondary outcomes will be assessed by comparing measurements before and after the intervention. Continuous outcomes (eg, viral load, mental health) will be analysed using paired t-tests. Logistic regression will be used to estimate the OR and 95% CIs for the association of self-reported adherence measures with VL suppression. Analysis will be conducted using STATA V.18, and statistical significance based on p<0.05.

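### The intention-to-treat approach promised in the abstract is not what the paired t-tests deliver: they leave out enrolled participants without a follow-up value, and the follow-up visit is not named

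*Protocol article*

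**What the plan says.** - **Principle.** The abstract (Methods and analysis) states "we will assess preliminary effectiveness using an intention-to-treat approach on HIV-related indicators and mental health outcomes", and names the visits as "at baseline, end intervention, 2-month follow-up during the 6-month implementation".
- **Contrast.** Data analysis, Quantitative data: "Secondary outcomes will be assessed by comparing measurements before and after the intervention".
- **Test.** The same section: "Continuous outcomes (eg, viral load, mental health) will be analysed using paired t-tests", with "statistical significance based on p<0.05". Intention-to-treat does not appear again.
- **Schedule.** Table 1 collects adherence and every mental health and well-being scale at months 0, 4 and 6. Viral suppression is collected at months 0 and 6 only.
- **Expected loss.** The Sample size section and Table 2 work with 90% of the 50 enrolled attending the month-6 assessment.
- **Drop-outs.** The Drop-outs section plans two call or visit attempts to participants who did not complete the intervention. The stated purpose is to learn why they left. Collecting outcomes is not mentioned.

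**The concern.** The article states an analysis principle and a test, and the two do not fit. In a single-arm study, intention-to-treat can only mean that everyone enrolled is analysed, whatever number of sessions they attended. A paired t-test without imputation keeps a poor attender who is assessed, but drops an enrolled participant who is not. It is a complete-pair analysis.

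Each paired test also uses two visits. In a month-6 comparison, someone assessed at months 0 and 4 and then lost contributes nothing, although the month-4 score is informative about where that person was heading.

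The within-person change is the only effect estimate this study will produce, and there is no comparison arm in which similar losses might offset it. The article says the sample is sufficient for preliminary effects and looks ahead to a randomised trial, so readers will use the estimate and may read the label as a guarantee that losses have been dealt with.

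**Working it through.** **1. The plan's own figures.** The stated precisions are 95% half-widths, 1.96 × √(p(1−p)/n).
- Retention, p = 0.90, n = 50: 0.083, stated as ±8%.
- Reach, p = 0.75, n = 67: 0.104, stated as ±10%.

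Both reproduce. No SD, effect size or power is stated for the paired t-tests, so nothing further can be reproduced.

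**2. Number left out.** 50 × 0.90 = 45 with a month-6 value. The month-6 paired test therefore uses at most 45 of 50 even if the retention target is met.

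**3. Size and direction of the bias.** Let d be the share without follow-up and f the true change of those lost divided by that of those assessed. Then

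change among assessed ÷ change among all enrolled = 1 / [(1 − d) + d·f].

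Here d = 0.10 comes from the protocol. The values of f and the larger losses are assumptions. The ratios are:

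- 10% lost: 1.11 for f = 0, then 1.05 for f = 0.5, then 1.00 for f = 1, and 0.95 for f = 1.5.
- 20% lost: 1.25 for f = 0, then 1.11 for f = 0.5, then 1.00 for f = 1, and 0.91 for f = 1.5.
- 30% lost: 1.43 for f = 0, then 1.18 for f = 0.5, then 1.00 for f = 1, and 0.87 for f = 1.5.

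Example for the first ratio: with d = 0.10 and f = 0 the denominator is 0.90, and its inverse is 1.11. At the planned loss the overstatement exceeds 11% only if those lost got worse.

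**4. Would a model using all visits help?** This is a simulation under assumed values: SD 5 at each visit; correlations 0.5 (months 0 and 4), 0.45 (months 0 and 6) and 0.7 (months 4 and 6); true change −3.0 at both follow-up visits; logistic drop-out on the change by month 4 with slope 0.2 per point; 11% missing at month 6.

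- Non-improvers leave, month 4 observed: paired −3.4, likelihood with all visits −3.0.
- Improvers leave, month 4 observed: paired −2.6, likelihood with all visits −3.0.
- Drop-out unrelated to change: paired −3.0, likelihood with all visits −3.0.
- Non-improvers leave, month 4 also missing: paired −3.38, likelihood with all visits −3.25.

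In the last case the model removes 0.13 of a bias of 0.38, about a third.

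**5. Scale against sampling error.** The SD of the month-6 change is 5 × √(2 × (1 − 0.45)) = 5.24. The standard error at n = 45 is 5.24/√45 = 0.78, and the 95% half-width is about 1.96 × 0.78 = 1.53. A bias of 0.4 points is about a quarter of that half-width.

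**The case against.** **Which parts of the case against stand**
- *The analyses are secondary and the study is not powered for efficacy.* This stands. It limits the consequence but does not remove the mismatch.
- *Analysis sets and missing-data rules may sit in an analysis plan that is not shown.* This also stands, and their absence is not the point here. The article itself states both the principle and the test.
- *All enrolled regardless of attendance is a fair single-arm meaning of intention-to-treat, and paired tests keep poor attenders.* This is true for anyone who is assessed. It does not cover enrolled participants with no follow-up value, and the plan expects about 5 of them.
- *A mixed model is one acceptable choice, not the only one.* This is fair. It also corrects fully only when drop-out depends on scores that were observed. The intervention runs to month 4, so someone lost during it may have neither follow-up value.

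**Stronger readings the documents do not support**
- A reader might infer that the third visit is ignored. The text leaves the follow-up visit unnamed, and separate month-4 and month-6 paired tests would fit it. For viral load there is no month-4 measurement to ignore.
- A reader might infer that the estimated change will be inflated because non-improvers leave. The documents say nothing about who leaves, and the planned calls and visits are meant to find that out. The bias can go up, down or be absent.

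**Conclusion.** The conflict is real: the intention-to-treat approach over three visits is not carried into the analysis section. The paired t-tests there use only participants with both values, and the follow-up visit is not fixed. At 90% retention about 5 of 50 enrolled drop out of the month-6 comparison.

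The consequence is a possible bias of unknown direction. It is about 11% upward if those lost had zero change, about 5% downward if they changed half as much again as those assessed, and nil if loss is unrelated to change. Those ratios rest on assumed values for the people lost. Only the 10% loss comes from the protocol. The effect grows if retention falls short of target.

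For a secondary, preliminary analysis this is moderate, but the change is worth making because it is cheap and the within-person change is the study's only effect estimate.

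**What to change.** 1. **Analysis set.** Define intention-to-treat here as all enrolled participants regardless of sessions attended, and carry that into the Quantitative data section.
2. **Main analysis for continuous outcomes measured at three visits.** Use a linear mixed model for repeated measures with visit as a categorical factor, unstructured covariance and all available data. Report the month-4 and month-6 changes from baseline with 95% CIs. Keep paired t-tests as a sensitivity analysis.
3. **Viral load.** It follows the two-visit schedule, so a third visit cannot help. Report it as a change from baseline to month 6 with the number analysed.
4. **Limits.** State that the model removes bias only when drop-out depends on observed scores, and only partly for participants lost before month 4.
5. **Minimum alternative.** If paired t-tests stay as the main analysis, name the visit compared, drop the intention-to-treat label and call the analysis complete-pair.

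The cost is wording in the abstract and the Quantitative data section. No extra visits, participants or data are needed, and the Stata version already named fits the model.

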**Discussion:**

We expect that the PM+Adherence will be acceptable and can feasibly be delivered by lay counsellors in resource-limited rural KwaZulu-Natal.

**Ethics and dissemination:**

Ethical clearance has been obtained from the University of KwaZulu-Natal Biomedical Research Ethics Committee, (BREC/00005743/2023). Dissemination plans include presentations at scientific conferences, peer-reviewed publications and community level.

STRENGTHS AND LIMITATIONS OF THIS STUDYCo-adaptation with adolescents and members of the community will provide culturally, contextually and age inclusive/appropriate adaptation of the Problem Management Plus intervention.This study will use existing implementation science theories, guided by the Medical Research Council framework for developing and evaluating complex interventions.The study is not powered to test the efficacy of the intervention; however, the sample size is sufficient for assessing feasibility, acceptability and preliminary effects.

## Introduction

 Mental health problems constitute a considerable health and disability-related burden worldwide, with young people bearing this burden,^1^,^3^ especially in middle-income countries, such as South Africa.^4^,^7^ In addition, the literature shows increased mental health problems in at-risk child and adolescent populations, such as orphanhood, exposure to violence and trauma, being ‘out of school’, socioeconomic disadvantages and high levels of deprivation.^6 7^ Another at-risk group for increased mental health problems are adolescents living with HIV (ALHIV). In addition to living with a chronic disease, ALHIV experience significant adversity related to stigma and discrimination coupled sometimes with parental illness and occasionally parental/family death, substance abuse, mental illness and living in impoverished communities.^8^,^11^ Despite antiretroviral treatment (ART) transforming HIV infection from inevitable death into a chronic condition,^12 13^ local literature highlights that the success of ART has not been without challenges, requiring daily dosing and sustained adherence to fully benefit from therapy.^14 15^ Incomplete adherence has been identified as an important driver of virological failure, drug resistance, and ultimately, progression to AIDS and death and is challenging in adolescents.^16^

ALHIV are disproportionately affected by and experience mental and behavioural health problems at higher rates than their non-HIV counterparts.^9 17^ Studies carried out in South Africa have found high rates of mental health problems, at a prevalence of 8%–12%,^18^,^20^ with increased engagement in risky behaviours among ALHIV.^8 21 22^ In addition, mental health problems have been found to adversely affect adherence to ART in this population, impacting clinical outcomes,^23 24^ with older adolescents (15–19) being the most affected.^24^ Despite the burden, the mental health needs of adolescents are often unaddressed; this is often perpetuated by low mental health awareness and literacy, limited access to mental health services as well inadequate services for adolescents and the cost of treating mental illnesses.^1 25 26^ Although an increasing number of studies have indicated a significant risk of poor behavioural outcomes that affect health and development in ALHIV, few evidence-based behavioural interventions exist to promote well-being and resilience in this population.^1721 27^,^29^ Well-being is the balance between an individual’s resource pool and the challenges they face while resilience refers to the capacity to maintain mental health despite exposure to adversity.^30 31^

A recent meta-analysis aimed to establish the differential impact of psychological interventions on mental well-being in clinical and non-clinical populations, reported that mindfulness-based and multicomponent positive psychological interventions had the greatest efficacy.^32^ They also found that positive psychological interventions, cognitive and behavioural therapy, and acceptance and commitment therapy were impactful; however, the effect sizes were moderate.^32^ The majority of the studies were from the Global North and involved general adult populations, which is not representative of the population of adolescents with HIV in South Africa.^32^ Two reviews by Bhana *et al*^21 33^ pointed out that despite the high rates of mental health problems in adolescent populations in low-middle-income countries(LMIC), there is still an urgent need to develop and evaluate evidence-based mental health treatments for ALHIV. One review^21^ examined the outcomes of interventions to support the mental health of adolescents living with or affected by HIV in LMICs. This review found seven studies conducted locally: five on HIV-affected adolescents^34^,^38^ and two on ALHIV.^11 39^ The two studies with adolescents aged 9–14 assessed the effects of a adapted 10-session family-based intervention called VUKA (‘Let’s wake up’ in isiZulu). VUKA is a culturally tailored cartoon storyline that facilitates family discussions and problem-solving to reduce risk behaviours in PHIV+youth in poverty-impacted areas.^11 39^ The intervention improved mental health, behaviour, treatment adherence and communication while stigma reduction was also noted.^11 21 39^ Another review by Bhana *et al* explored current (2014–2020) evidence-based mental health interventions for young people living with HIV or affected by HIV.^33^ Of the 13 studies identified, only 8 focused on ALHIV, with interventions varying from group-based and family-strengthening interventions to psychoeducation and disclosure. This review concluded that although there are some promising approaches, more work is needed to identify evidence-based approaches and the corresponding mechanisms of change for this population.^33^ These reviews underscore the need for brief, simple, evidence-based transdiagnostic mental health interventions for low-resource settings and task-shifting approaches owing to limited human resources.^21 33^ Despite the push to increase access to mental health counselling in South Africa, especially in primary health care,^40 41^ anecdotal findings show that adolescents rarely use health services offered on the primary care platform.^42^ Evidence suggests that at-risk adolescents globally and in South Africa underuse mental health services,^42 43^ and where youth-friendly clinics are available, they do not offer mental health support.

WHO’s Problem Management Plus (PM+)^44 45^ was identified as an appropriate intervention to address psychological distress because of its transdiagnostic and low-intensity nature. It also does not require specialists to facilitate, making it suitable for resource-limited settings. We aim to contribute to addressing this gap by culturally and contextually co-adapting PM+^44^ for use with ALHIV in rural South Africa with an additional adherence component (PM+Adherence) to address adherence concerns to ART that are common among this targeted population. In addition, we will conduct a hybrid type 3 implementation study focused on implementation outcomes to assess (1) feasibility and acceptability of PM+Adherence with ALHIV in rural South Africa and (2) evaluation of patient outcomes related to HIV and mental health.

### The intervention

PM+ was designed to be delivered face to face by trained non-specialists in five 90 min weekly sessions. The intervention takes participants through four evidence-based core strategies: stress management, problem-solving, behavioural activation and strengthening social support.^44^ The therapeutic aim of the intervention is to help deal with common mental health problems (eg, depression, anxiety and stress) and improve the management of practical problems. PM+ was developed to be facilitated individually but can also be carried out in group format.^46^ Both the individual and group versions have been found to be effective.^47^ In discussion with a local youth trial board, young people thought individual sessions would be more beneficial with group sessions to be considered after implementation if needed. Although initially developed for adult populations facing adversity, few studies assess its adaptation and utility in young people.^48 49^

### Adaptation

Despite the paucity of evidence on locally developed psychological interventions, the literature highlights the benefits of adapting interventions to promote the applicability of core principles to various contexts, thereby making them more universally available.^50^ Hall *et al* suggest that cultural and contextual adaptations are warranted when community-specific cultural contexts of risk and resilience influence disorder, and these contexts should guide efforts to design and evaluate adapted interventions.^51^ Heim *et al* highlighted the importance of adaptations made to the PM+ intervention, such as the names of the main characters and case studies, to make them locally meaningful.^52^ Additionally, they found that the adaptation of PM+ in Kenya integrated storytelling as an important feature. In Pakistan, the language was adapted to be more direct as Urdu is more direct than English (eg, phrases such as ‘we are interested in finding out’ were changed to ‘we want to know’). Culturally relevant religious practices were included in the adaptation of Pakistan and Kenya. Another adaptation in Kenya included the role of the family, in which the family was contracted to support treatment compliance.^52^

## Methodology and analysis

The first phase of this study will be a realist synthesis to identify and refine a programme theory that explains how and why WHO’s PM+ works. A realist synthesis reviews evidence to understand how, for whom and under what circumstances complex interventions function in complex environments.^53 54^ This approach was chosen because it explicitly explains how and why contexts influence outcomes and the processes/mechanisms at play.^55^ The second phase will culturally co-adapt PM+ to the local context. In the third phase, a feasibility study will examine the implementation outcomes while collecting data to evaluate patient outcomes of the culturally co-adapted PM+Adherence intervention among ALHIV.

### Study setting

KwaZulu-Natal (KZN) is one of the poorest provinces in South Africa, with high youth unemployment and HIV prevalence.^56^,^58^ Adolescents comprise approximately 11.3 million in the country, of which 2.1 million are found in KwaZulu-Natal.^59^ Although the total number of persons living with HIV (PLHIV) in South Africa increased from an estimated 3.68 million in 2002 to 8.45 million by 2022, the prevalence among the youth aged 15–24 has seen a slight decline from 6.24% in 2002 to 5.79% 2022.^59^ A community-based HIV study in KZN found that the prevalence among adolescent girls was 11.5% and 5.0% among adolescent boys aged 15–19^57^.

The study will be conducted in the uMkhanyakude (rural) district of the KZN Province, South Africa. uMkhanyakude is characterised by poverty, unemployment, poor infrastructure and temporary local migration, with family members dependent on small-scale agriculture and allowances from migrant workers and government grants. uMkhanyakude is one of the poorest districts in South Africa, with a high HIV prevalence of more than 40% and poor access to resources, with approximately 22% of the population having access to piped water and sanitation. This study is embedded within the Africa Centre Demographic Information System (ACDIS) cohort in rural KwaZulu-Natal, South Africa, established in 2000 by the Africa Health Research Institute (AHRI).^60^ AHRI is an independent, transdisciplinary scientific research institute based across two campuses in the South African province of KZN.

### Phase 1: rapid qualitative assessment

#### Study design and participants

Using the collaborative Design, Implementation, Monitoring and Evaluation approach,^61^ NN and [name] will train research staff with a minimum honours degree to conduct group free-listing interviews, in-depth interviews and participatory group discussions with ALHIV, their caregivers and healthcare professionals (HCPs). Free-listing interviews are a simple paper-and-pencil technique that makes it possible to identify, measure and describe variation in cultural knowledge between groups^62^ while establishing the coherence or boundedness of particular cultural domains to identify the items belonging to those domains and discern which items are more salient or representative of the domain.^63 64^ These will be conducted in groups which will facilitate recall and discussion on the different terminologies. We will use free lists to explore the local expressions, concepts and terminologies of mental health problems affecting ALHIV. In-depth interviews will be used to gather detailed information about the expressions, concepts and terminologies of mental health mentioned during the free-listing interviews to understand better how ALHIV conceptualise mental illness and how they navigate these mental health issues. Participatory group discussions will be built from the free lists and in-depth interviews to better understand the issues experienced by the ALHIV, help identify behavioural strategies of adherence commonly used by adolescents and explore the gender and potential age differences that might need to be considered in the intervention.

